**Objective:**

This study aims to explore the trial design and effects of 3Scape videos on older adults’ symptoms of depression and anxiety and the efficacy of this technology in improving the quality of life of patients attending the Short-Term Assessment, Rehabilitation, and Treatment Psychiatry Day Hospital program at Glenrose Rehabilitation Hospital and to provide data to estimate the parameters required to design a definitive randomized controlled trial.

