### Evaluation Objectives and Research Questions

This study aims to explore the trial design and effect of 3Scape videos on older adults’ depressive and anxiety symptoms and quality of life and the efficacy in terms of caregiver burden of the Short-Term Assessment, Rehabilitation, and Treatment Psychiatry Day Hospital program at Glenrose Rehabilitation Hospital and to provide data to estimate the required parameters to design a definitive randomized controlled trial (RCT). Thus, this study has the following five research questions:

Is the designed protocol feasible for conducting a future definitive RCT?Do the 3Scape videos affect older adults’ depressive and anxiety symptoms, mood, and overall quality of life compared with clients who receive the standard of care?What are the overall experiences, beliefs, and attitudes of older adults while watching 3Scape videos?What are the overall experiences, beliefs, and attitudes of therapists while watching 3Scape videos?Do 3Scape videos affect caregivers’ burden compared with the same caregivers who provide the standard of care?

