### Outcome Variables

#### Research Questions 1-2 (Primary Outcome Variables)

Older adults’ depressive and anxiety symptoms, mood, overall quality of life, and engagement are the primary outcome variables for these research questions. Older adults’ depressive and anxiety symptoms will be assessed using the Generalized Anxiety Disorder-7 item (GAD-7) scale patient self-report tool [21] and the Health of the Nation Outcome Scale (HoNOS; a clinician rating tool) symptoms [22], older adults’ mood will be measured using PANAS (20-item self-report questionnaire) [23], and older adults’ overall quality of life will be measured using Older People’s Quality of Life-Brief (OPQoL-Brief) questionnaire scale-13 items self-reported tool [24].

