**Primary outcome**																					
	GAD-7^a^	Older adults		GAD-7 scale		✓^b,c,d^		✓^c,d^		✓^d^		✓^d^		✓^d^		✓^d^		✓^d^		✓^c,d^	
	HoNOS^e^	Older adults		HoNOS, a clinician rating tool		✓^c,d^		✓^c,d^		✓^d^		✓^d^		✓^d^		✓^d^		✓^d^		✓^c,d^	
	OPQoL-Brief^f^	Older adults		OPQoL-Brief scale		✓^c,d^		✓^c,d^		✓^d^		✓^d^		✓^d^		✓^d^		✓^d^		✓^c,d^	
	PANAS^g^	Older adults		PANAS		✓^c,d^		✓^c,d^		✓^d^		✓^d^		✓^d^		✓^d^		✓^d^		✓^c,d^	

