### Data Analyses

#### Research Questions 1, 2, and 3

The analyses will be conducted in SPSS using intention-to-treat principles. Descriptive statistics will be used to characterize the groups during the pretest. Owing to the small sample size, comparisons of the GAD-7, HoNOS, OPQoL-Brief, and PANAS scores within the groups will be performed using a Wilcoxon signed-rank test (*P*≤.05), and comparisons between the groups will be calculated using the Mann–Whitney *U* test (*P*≤.05). The GAD-7, HoNOS, OPQoL-Brief, and PANAS scores will be used to analyze the clinical significance, established as a change of 2 or more units [30]. Participants’ engagement will be analyzed using descriptive statistics.

#### Research Question 4

The audiotapes will be transcribed and content analysis will be performed. The content analysis will be data driven. Data codes will be inductively generated using the data collected. Through the coding, a small number of themes or categories will be generated. The analyses will be performed by an RA, and a consensus in the interpretations will be achieved through a discussion among the research team members. The validity of the interpretations will be discussed with and agreed upon by every member of the research team. NVivo 10 software will be used to conduct data analysis.

#### Research Question 5

Descriptive statistics will be used to characterize the groups at pretest and posttest. Owing to the small sample size, comparisons of the MBI-HSS MP scores within the groups will be performed using a Wilcoxon signed-rank test (*P*≤.05), and comparisons between the groups will be calculated using a Mann–Whitney *U* test (*P*≤.05).

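### Depressive symptoms are the first-named primary outcome under research question 2, but no depression-specific measure or separately analysed depression endpoint is defined

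*Protocol article*

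**What the plan says.** Depression leads the list of effects wherever the article states them. The abstract's objective refers to "effects of 3Scape videos on older adults’ symptoms of depression and anxiety". Research question 2 asks: "Do the 3Scape videos affect older adults’ depressive and anxiety symptoms, mood, and overall quality of life". The primary outcome section for research questions 1-2 opens: "Older adults’ depressive and anxiety symptoms, mood, overall quality of life, and engagement are the primary outcome variables for these research questions".

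That section then assigns instruments to constructs:

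- Depression and anxiety together: "Older adults’ depressive and anxiety symptoms will be assessed using the Generalized Anxiety Disorder-7 item (GAD-7) scale patient self-report tool", continuing "and the Health of the Nation Outcome Scale (HoNOS; a clinician rating tool) symptoms".
- Mood: "older adults’ mood will be measured using PANAS (20-item self-report questionnaire".
- Overall quality of life: OPQoL-Brief.

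Table 1 lists GAD-7, HoNOS, OPQoL-Brief and PANAS as the primary outcome rows. It describes the second only as "HoNOS, a clinician rating tool". Data Collection Methods administers these same four.

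Data Analyses compares the four sets of scores within groups (Wilcoxon signed-rank) and between groups (Mann-Whitney), and adds: "The GAD-7, HoNOS, OPQoL-Brief, and PANAS scores will be used to analyze the clinical significance", with a change of 2 or more units as the criterion.

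**The concern.** A primary outcome needs an instrument whose score can be read as that outcome. Here depression and anxiety are treated as one construct. The only self-report tool given to that construct is named for anxiety, and the other is a clinician rating whose relevant part is not identified.

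Two things are at stake.

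- **Interpretation.** Because GAD-7 is declared to assess both symptom types, a GAD-7 difference, or a 2-unit GAD-7 change counted as clinically significant, could be reported as an effect on depressive symptoms. An undifferentiated HoNOS change could be reported in the same way.
- **Planning.** The study is meant to supply parameters for a definitive trial, and the Discussion says its estimates can be used for later sample size calculations. If depression is to be an endpoint of that trial, the pilot should deliver a standard deviation, a completion rate and a rough effect estimate for an identified depression measure. None is identified.

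**Working it through.** The point turns on which instrument is tied to which outcome, so the main check sets the sections side by side.

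**Step 1: construct to instrument to analysis**

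| Primary construct | Instrument assigned (Outcome Variables) | Row in Table 1 | Score analysed (Data Analyses) |
|---|---|---|---|
| Depressive symptoms | GAD-7 and HoNOS, jointly with anxiety | no row labelled depression | GAD-7 scores, HoNOS scores |
| Anxiety symptoms | GAD-7 and HoNOS, jointly with depression | GAD-7, HoNOS | GAD-7 scores, HoNOS scores |
| Mood | PANAS | PANAS | PANAS scores |
| Overall quality of life | OPQoL-Brief | OPQoL-Brief | OPQoL-Brief scores |

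Four scales are analysed. Two are assigned to the joint construct, one to mood and one to quality of life: 2 + 1 + 1 = 4. That leaves 4 − 4 = 0 assigned to depression alone.

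**Step 2: can either joint instrument separate depression?**

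- GAD-7: the name the article gives is an anxiety scale, and the article offers no reason to read its score as depression.
- HoNOS: the article calls it a clinician rating tool and gives no items. The word 'symptoms' after its name in the outcome section might point to a symptom component. No component is defined, and the word does not recur for HoNOS in Table 1, Data Collection Methods or Data Analyses. Even on that reading the component would still carry depression and anxiety together, because the sentence assigns both to it.

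**Step 3: can PANAS or OPQoL-Brief fill the gap?** Not on the article's own terms. It lists mood and quality of life as outcomes distinct from depressive symptoms and gives each its own scale.

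**Step 4: does the sample size point to a planned depression endpoint?** The stated inputs are power 0.80, α 0.05 and effect size 1.20. For a two-sided two-sample t test with n per group:

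- noncentrality = 1.20 × √(n/2), degrees of freedom = 2n − 2
- n = 12: noncentrality = 1.20 × √6 = 2.94, df = 22, power = 0.802
- 12 is the smallest n reaching 0.80, so the total is 24
- dropout: 24 / (1 − 0.20) = 30

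The stated 24 and 30 reproduce. The effect size is not tied to any outcome, so the calculation does not reveal a depression endpoint that the text leaves out.

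**The case against.** The strongest reply is that HoNOS is assigned to depressive and anxiety symptoms in the same sentence as GAD-7, is a primary outcome in Table 1, is given in both arms and is analysed. A reader might infer that no listed scale measures depression at all. The documents do not support that: they do not give the content of HoNOS, so they cannot show that depression is absent from it. Nor do they say that HoNOS is analysed as a total; the wording is only HoNOS scores. This part of the reply stands.

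A reader might also infer that the trial cannot answer its lead question. That fails too. Research question 1 is feasibility, and the Discussion calls feasibility the primary objective. Depression is one element of research question 2, beside anxiety, mood and quality of life, for which scales are assigned.

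A third reply is that the choice of HoNOS item or subscale, and its scoring, commonly belongs in a full protocol or SAP that is not shown. That is fair for scoring detail. It does not cover the assignment the article itself makes, in which an anxiety scale is declared to assess depression. If depression was to be measured by a scale that is not in the battery, no later analysis document could recover it.

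Finally, GAD-7, HoNOS and OPQoL-Brief are already given at the start and end of the program as standard care. That is a sensible reason for a 30-person feasibility study to use them. It explains the choice of instruments but does not justify attaching a depression claim to GAD-7.

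**Conclusion.** The point holds as a mismatch between a named primary outcome and its measurement. Depressive symptoms come first among the research question 2 outcomes, yet none of the four analysed scales is dedicated to them and no depression component or endpoint is named. A depression effect, and the corresponding parameters for the definitive trial, cannot be separately identified from the plan as written.

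The consequence is confined to what may be claimed about depression. The feasibility objective and the anxiety, mood and quality-of-life comparisons are not affected by this point. The size is a matter of claims, not of a number: the sample size reproduces and is not in question here.

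The conclusion rests on the article's own naming of GAD-7 as an anxiety scale and on the absence of any named depression score in the outcome, schedule and analysis sections. It assumes nothing about what HoNOS contains. If a full protocol already names a HoNOS depression component as an analysed variable, what remains is to correct the statement about GAD-7. The change should be made, but it carries no safety consequence.

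**What to change.** First, state that GAD-7 measures anxiety only. Then choose one of these:

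1. **Name the HoNOS component that carries depression, if it has one,** as the depression endpoint, and analyse and report it separately from anxiety and from any other HoNOS score. This adds no assessment time. It depends on the scale having a usable component, which the team must confirm.
2. **Remove depressive symptoms** from the objective, research question 2, the primary outcomes and the conclusions, leaving anxiety, the clinician rating, mood and quality of life. This is a change of wording, and the price is a narrower claim.

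Optionally, and in place of either, add one short validated self-report depression scale in both arms at T0, T1 and T8 (weeks 0, 12 and 18), the three time points Table 1 shows for both groups, and name it as the depression endpoint. This would give the definitive trial a directly usable standard deviation and completion rate. It adds a small burden to a battery of about 30 minutes and needs an ethics amendment. The article reports a launch in April 2020 followed by a hold, and does not say whether anyone was enrolled before it; anyone who was could lack a baseline value on the new scale.

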#### Research Questions 1-2 (Secondary Outcome Variables)

Engagement while watching the 3Scape videos will be measured using an engagement scale developed by team members in a previous study [25]. This is an 8-point Likert scale that has been shown to be understood by older adults, even those with mild cognitive impairments.

#### Research Question 3 (Participants: Older Adults)

Participants will be asked to participate in a postsurvey to provide feedback on their experiences while watching the 3Scape videos. The overall experience, beliefs, and attitudes of older adults while watching the 3Scape videos will be measured using an instrument (height items 5-point Likert scale and 4 open-ended questions) developed by the University of Calgary in a previous study on this technology.

#### Research Question 4 (Participants: Therapists)

Participants will be asked to participate in a poststudy interview to provide feedback on their experiences, with their patients using the 3Scape videos*.*

#### Research Question 5 (Participants: Therapists)

The caregiver burden will be assessed by using the burnout and workload perception among health care providers, measured by the Maslach Burnout Inventory-Human Services Survey for Medical Personnel (MBI-HSS MP) [26].

All of the measures have good to excellent metric properties [27,28].

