We believe that older adults can benefit significantly from information and telecommunication technologies as a strategy for improving mental health conditions such as depression and anxiety, while simultaneously improving their quality of life. Information and telecommunication technologies have the potential to improve the delivery of reminiscence therapy, as these technologies facilitate access to and the selection of biographical information and related contents, or by providing novel multimodal interaction forms (eg, virtual reality) to trigger memories [9,10]. Previous investigations have studied the impact of information and telecommunication technologies on reminiscence therapy on the quality of caregiver and patient relationships, subjective patients’ well-being [11], alleviating depressive symptoms in older adults [12], and supporting social interactions in residential care [13]. 3D immersive technologies (or immersive technologies) such as virtual reality and 3D display have also been shown to have a variety of positive effects on the mental, emotional, and social health of older adults [14]. In addition, there is an opportunity to indirectly reduce caregiver and health care professional burden by delivering stimulating viewing content to older adults affected by mental health conditions, thereby enhancing their daily experience. Although these immersive technologies are slowly becoming more accessible (ie, in terms of cost), there is a lack of literature on the benefits of 3D immersion technology for the mental health well-being of seniors. As a result, whether 3D immersion technology has a positive effect on older adults’ mental health conditions and the burden of self-care remains an open question.

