**Figure 1 figure1:**
[figure not shown]
Study components. GRH: Glenrose Rehabilitation Hospital; HoNOS: Health of the Nation Outcome Scale; MoCA: Montreal Cognitive Assessment; OPQoL-Brief: Older People’s Quality of Life-Brief; RCT: randomized controlled trial.

Research questions 1-3, feasibility parallel-group RCT: The experimental group will receive the intervention, which consists of sessions with the 3Scape videos, whereas the control group will receive the standard of care used at the Short-Term Assessment, Rehabilitation, and Treatment Psychiatry Day Hospital program at Glenrose Rehabilitation Hospital (see the *Outcome Variables* section for more details). For this pilot study, we will follow the CONSORT (Consolidated Standards of Reporting Trials) guidelines for randomized feasibility studies [17]. The *Methods* section is presented with regard to the objectives of the study.Research question 4, study design: qualitative description design [18].Research question 5, study design: quantitative descriptive [19].

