#### Research Questions 4-5 (Participants: Therapists)

We aim to recruit 5-10 therapists participating in the Short-Term Assessment, Rehabilitation, and Treatment Psychiatry Day Hospital program who provided the intervention.

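### The aim claims efficacy on caregiver burden, but Research Question 5 is an unrandomised description of burnout in 5-10 treating therapists and cannot support that claim

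*Protocol article*

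**What the plan says.** The aim in Evaluation Objectives and Research Questions includes "the efficacy in terms of caregiver burden of the Short-Term Assessment, Rehabilitation, and Treatment Psychiatry Day Hospital program". Research Question 5, in the same section, reads: "Do 3Scape videos affect caregivers’ burden compared with the same caregivers who provide the standard of care".

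Study Design (text under Figure 1) assigns Research Questions 1-3 to the randomised feasibility trial and treats the fifth apart: "Research question 5, study design: quantitative descriptive".

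Under Outcome Variables, Research Question 5 (Participants: Therapists), the outcome is defined: "The caregiver burden will be assessed by using the burnout and workload perception among health care providers". The instrument named for this is the MBI-HSS MP, and no other burden instrument appears.

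Under Sample Size, Research Questions 4-5: "We aim to recruit 5-10 therapists participating in" the day hospital program, restricted to therapists who delivered the intervention.

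Data Analyses, Research Question 5, plans a Wilcoxon signed-rank test within groups and a Mann–Whitney U test between groups, both at P≤.05.

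Background and Rationale speaks of "an opportunity to indirectly reduce caregiver and health care professional burden", which names caregivers and professionals side by side as two groups.

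**The concern.** The aim and the research question are worded as a question of effect. The component meant to answer them has no randomisation and no comparison group, and its only respondents are staff who delivered the videos. A P value from it, read against the stated aim, would invite the conclusion that the videos do or do not reduce caregiver burden. A reader who has met the Background's distinction between caregivers and professionals could also take the result to concern family or informal caregivers, none of whom is enrolled. What is at stake is what the trial may conclude on this question. Allocation, the patient sample size and the patient outcomes are unaffected.

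**Working it through.** The protocol gives no power or sample-size figure for Research Question 5, only the target of 5-10 therapists. Its calculation of 24 participants, raised to 30, concerns the older adults and has no bearing here. The check is therefore mainly a comparison of sections.

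**1. Claim against design.** The aim says efficacy and the question asks whether the videos affect burden. The design label is descriptive and sits outside the randomised part. An effect needs a contrast between what happened with the videos and what would have happened without them. The question's own contrast is each provider with himself or herself. At best that is an uncontrolled before-after change, in which the videos cannot be separated from anything else that changes over the same weeks.

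**2. Analysis against sample.** A Mann–Whitney test needs two independent groups. Every recruited therapist delivered the intervention, so there is one group, and the planned between-group comparison has no second sample.

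**3. Timing.** Three places describe when the MBI-HSS MP is given:
- Data Collection Methods, Research Question 5: pretest and posttest.
- Participant Timeline, end of the Control Group subsection: week 12 (T1), with no other visit.
- Table 1: a single tick, apparently in the last column (T8).

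T1 is defined for patients as the visit before the videos start, and T8 as the posttest at week 18. Taken together, the second and third entries could make up the pre-post pair in the first, but neither says so. Under either one alone no paired change exists, and the Wilcoxon test cannot be computed.

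**4. What the within-therapist test could show if both time points are collected.** With n non-zero, untied differences, the smallest exact two-sided Wilcoxon P value is 2/2^n:
- n = 5: 2/32 = 0.0625
- n = 6: 2/64 = 0.031
- n = 10: 2/1024 = 0.002

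At n = 5 the exact test cannot reach .05 whatever the data. This depends on using the exact test. With all five differences in one direction, the normal approximation without continuity correction gives z = (15 − 7.5)/√(5×6×11/24) = 7.5/√13.75 = 2.02, P about 0.043. The protocol does not say which version applies.

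No effect size is given for this question. For assumed standardised paired changes of 0.5, 0.8 and 1.2 (normal differences, exact test, 20,000 simulated samples), power is:

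| Therapists | 0.5 | 0.8 | 1.2 |
|---|---|---|---|
| 5 | 0 | 0 | 0 |
| 6 | 0.11 | 0.24 | 0.48 |
| 8 | 0.19 | 0.44 | 0.77 |
| 10 | 0.28 | 0.61 | 0.91 |

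So a non-significant result would say little across most of the planned range, and a significant one would still be an uncontrolled change.

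**The case against.** The strongest reply is that the protocol defines its terms. Research Question 5 refers to caregivers who provide the standard of care; standard care here is nursing, medication management and group therapy delivered by the program; and the outcome heading says the participants are therapists. On that reading caregiver means treating provider, and 5-10 of them are measured. This stands. A reader might infer that the construct is measured in nobody, or that the trial can say nothing at all about caregiver burden in any sense. The documents do not support that: a descriptive statement about burnout in these therapists is possible if both time points are collected. What remains is that the aim does not carry this definition and uses the word efficacy.

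A reader might also infer that the videos are too small a part of a therapist's work to move a burnout score. The documents do not allow this to be sized. They give no rota for who leads the sessions and no therapist workload, and the 36 hours per 6 weeks under Control Group are hours received by a patient.

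The abstract's Objective gives as its efficacy target "the efficacy of this technology in improving the quality of life of patients" and omits caregiver burden. That can be ordinary condensing, and the point does not rest on it.

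Finally, Principal Findings gives feasibility as the primary objective, so this question is peripheral, and the outcome section openly states what is measured. Both are fair and limit the consequence. They do not remove the conflict between an efficacy aim and a descriptive design.

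**Conclusion.** The concern holds as a mismatch between claim and design. One unrandomised group of 5-10 therapists, all of whom delivered the videos, assessed with a burnout inventory, can at most yield a description of burnout in those therapists. It cannot support an efficacy or causal statement on caregiver burden, or any statement about family or informal caregivers.

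This rests on the sections as printed and on no assumption about the instrument's content or the therapists' workload. The size is not a number to be corrected: there are no comparison therapists for a planned two-group test, and there are three accounts of timing for one instrument. The P-value floor of 0.0625 applies to the exact test at 5 therapists, and the power figures depend on assumed effect sizes. Both are supporting detail.

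**What to change.** - **Aim** (Evaluation Objectives and Research Questions): delete the efficacy claim on caregiver burden and keep the description of the setting.
- **Research Question 5**: reword as an exploratory description of MBI-HSS MP burnout scores in the therapists who deliver the video sessions.
- **Outcome Variables, Research Question 5**: rename the outcome therapist burnout.
- **Data Analyses, Research Question 5**: drop the Mann–Whitney comparison. Report any within-therapist change descriptively, for example as individual values with median and range, and draw no efficacy conclusion.
- **Timing**: reconcile Table 1, the therapist sentence in Participant Timeline and Data Collection Methods. A before-after description needs both time points.

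The cost is rewording, plus making sure that both assessments are scheduled, as Data Collection Methods already intends. The downside is one fewer efficacy claim.
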